**Methods:**

The study will use a randomized, single-blind, sham-controlled design to investigate the treatment efficacy of motivational nondirective resonance breathing (MNRB™) and transcutaneous vagus nerve stimulation (Nemos® tVNS) on patients diagnosed with FM. Consenting FM patients (*N* = 112) who are referred to the Department of Pain Management and Research at Oslo University Hospital, in Oslo, Norway, will be randomized into one of four independent groups. Half of these participants (*N* = 56) will be randomized to either an experimental tVNS group or a sham tVNS group. The other half (*N* = 56) will be randomized to either an experimental MNRB group or a sham MNRB group. Both active and sham treatment interventions will be delivered twice per day at home, 15 min/morning and 15 min/evening, for a total duration of 2 weeks (14 days). Participants are invited to the clinic twice, once for pre- and once for post-intervention data collection. The primary outcome is changes in photoplethysmography-measured heart rate variability. Secondary outcomes include self-reported pain intensity on a numeric rating scale, changes in pain detection threshold, pain tolerance threshold, and pressure pain limit determined by computerized pressure cuff algometry, blood pressure, and health-related quality of life.

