## Methods/design

### Aim

The primary aim of this protocol article is to describe the design of a randomized controlled clinical trial investigating the effects of motivational nondirective resonance breathing (MNRB) and transcutaneous vagus nerve stimulation (tVNS) on photoplethysmography (PPG) measured heart rate variability (HRV) in patients diagnosed with FM. Secondary outcomes are changes in self-report numeric rating scale (NRS) pain intensity, pain detection threshold (PDT), pain tolerance threshold (PTT), and pressure pain limit (PPL) determined by computerized cuff-pressure algometry (CPA), blood pressure (BP), and health-related quality of life. The principal objective is to explore the following four research questions:
Does a standardized sham-controlled tVNS intervention or MNRB intervention have effects upon PPG- measured HRV?Is a substantial change in HRV associated with a significant change of self-report NRS pain intensity?Is a substantial change in HRV associated with a change in computerized cuff-pressure algometry PDT, PTT, and/or PPL?Are there changes in BP following either an active or sham tVNS intervention and/or a MNRB intervention?Are there effects on health-related quality of life and behavior following either an active or sham tVNS intervention and/or a MNRB intervention?

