#### Statistical considerations and sample size calculation

An independent trial statistician who is blinded to the treatment allocation will complete the initial analysis for the main outcomes. Data analyses will be performed using IBM SPSS version 25, R software, and SAS® software after importing data from Viedoc. To sufficiently detect a difference between groups in HRV as it relates to NRS pain intensity, a sample size between 30 and 77 (depending on the HRV metric used) is typically needed [54]. However, subgroups are commonly employed within designs that have been suggested to require 20 participants per cell [55]. Furthermore, researchers have typically used Cohen’s calculations of small (0.2), medium (0.5), and large (0.8) effect sizes when quantifying the magnitude of group differences for HRV investigations. However, it has been recommended that these guidelines should only be used when the effect size distribution (ESD) is unknown; analyses have shown that Cohen’s guidelines underestimate the magnitude of small and large effect sizes and that HRV studies are generally underpowered [56]. A change on the NRS of 20% as our secondary outcome measure in this study for participants between CVI and CVII will be considered to be a clinically significant treatment efficacy [57, 58].

Due to our power calculation and in light of these findings, effect sizes of 0.25, 0.5, and 0.9 should be interpreted as small, medium, and large effects (after rounding to the closest 0.05). To achieve a statistical power of 0.8 to detect a large effect size, 21 participants are required per group in a case-control study [56]. However, in order to account for possible participant dropout, 28 participants per group will be included which correlates to a statistical power of 0.9. This recommended sample size which is based upon the aforementioned ESD can be tailored to our specific study used to appropriately power this research investigation [56]. This makes it more likely to better replicate and derive true effect size estimates. Mean with standard deviation or median with interquartile will be reported for continuous variables/data. Frequency and percentage will be given for categorical variables/data.

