Missing data will be treated as follows: If the first (morning pre-intervention) NRS/HRV recording is missing, the last (evening post-intervention) NRS/HRV recording will be used from the night before. If the second (morning post- intervention) NRS/HRV recording is missing, then the first (morning pre-intervention) NRS/HRV recording will be used. If the third (evening pre-intervention) NRS/HRV recording is missing, then the first (morning pre- intervention) NRS/HRV recording will be used. Finally, if the last (evening post-intervention) NRS/HRV recording is missing, then the third (evening pre-intervention) NRS/HRV recording will be used. If all morning and evening NRS/HRV recordings are missing from a day, then NRS/HRV recordings from the day before will be used based upon the assumption that improvement/change is not present. The patient-reported outcome measures will be modeled by repeated measures and fitting random effects models with random slopes. Random effects models are considered the gold standard when analyzing repeated measures and handling missing data in longitudinal design [59, 60].

Baseline characteristics as mean with standard deviation or median with interquartile and frequency with percentage will be described for the four participant groups, active and sham. The change from the first to second data points will be calculated for the 14-day treatment session in regard to HRV and NRS present pain intensity. The change from CVI to CVII HRV, NRS present pain intensity, and NRS average pain intensity will be determined. Difference in changes between the groups in the morning session and evening session will be examined and tested by using two-way analysis of variance (ANOVAs) or random intercept and slope models. For overall difference in the changes between the four groups regardless of morning, evening or days, random intercept models or repeated one-way analysis of variance (ANOVAs) will be used to analyze the data. The tests will be two-sided, and the significance level will be set to 0.05.

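### The between-group tests stated for HRV change do not match the sham-controlled question or the two-group sample size, and none is clearly tied to the visit-to-visit change

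*Protocol article*

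**What the plan says.** All places are in the Protocol article.

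- **Outcome (Abstract, Methods).** "The primary outcome is changes in photoplethysmography-measured heart rate variability". No timepoint is attached to it there.
- **Question (Aim).** The first research question is "Does a standardized sham-controlled tVNS intervention or MNRB intervention have effects upon PPG- measured HRV".
- **Sample size (Statistical considerations and sample size calculation).** "effect sizes of 0.25, 0.5, and 0.9 should be interpreted as small, medium, and large effects". For a large effect, 21 per group gives power 0.8 in a case-control comparison. Enrolling 28 per group allows for dropout and is linked to power 0.9.
- **Change scores (same section).** "The change from the first to second data points will be calculated for the 14-day treatment session". The CVI-to-CVII change in HRV is also to be determined.
- **Tests (same section).** Differences in change between groups in the morning and evening sessions are "tested by using two-way analysis of variance (ANOVAs) or random intercept and slope models". Then comes the overall test: "For overall difference in the changes between the four groups regardless of morning, evening or days, random intercept models or repeated one-way" analysis of variance. Finally, "The tests will be two-sided, and the significance level will be set to 0.05".

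No active-against-sham contrast is named, no test is labelled primary, and no division of the 0.05 is given.

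**The concern.** The question and the sample size both concern an active arm against its own sham. The overall test asks something else, namely whether any of four groups differ. A modality difference is plausible by design: both MNRB arms follow a paced-breathing program and both tVNS arms breathe normally (Description of intervention arms). A significant four-group result could therefore arise with neither treatment beating its sham.

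The quantity under test matters too. The test wording refers to morning and evening sessions and to days, which describes home recordings. Once treatment has started, a session's pre-treatment reading already carries the effect of earlier sessions. A sustained rise in resting HRV lifts both readings and drops out of their difference. The clinic-visit change would show it, but no test is clearly linked to that change.

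Finally, each participant can supply up to 28 session changes. The two-way ANOVA option has no repeated-measures wording. The same section describes random effects models as the best standard for repeated measures, so offering an ANOVA in their place sits badly with its own reasoning.

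**Working it through.** **Inputs from the article.** Four arms of 28; standardised effect 0.9; two-sided 0.05; 28 home sessions (Design). **Assumed, because the article gives no figure:** modality difference, within-participant correlation of session changes, variance shares.

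**1. The plan's own figure.** Two-sample t-test, noncentrality δ = d√(n/2), df = 2n − 2.
- n = 21: δ = 0.9 × √10.5 = 2.92, df 40, power 0.812. (n = 20 gives 0.792.)
- n = 28: δ = 0.9 × √14 = 3.37, df 54, power 0.911.

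The stated 21 and 28 are reproduced, as a two-group comparison.

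**2. The four-group test.** Noncentral F with 3 and 108 df, λ = n Σ(mean − grand mean)², critical value 2.69.
- Both tVNS arms 0.5 SD from both MNRB arms, active equal to sham: deviations ±0.25, λ = 28 × 4 × 0.0625 = 7.0, rejection probability 0.572.
- The same pattern at 0.9 SD: λ = 28 × 4 × 0.2025 = 22.68, rejection probability 0.985.
- Both active arms 0.9 SD above their shams, no modality difference: again λ = 22.68 and 0.985.

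The last two cases give the test the same λ, so a significant result cannot tell them apart.

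**3. A sustained effect.** If treatment adds s to both readings of a session, the change is (post + s) − (pre + s) = post − pre, and s disappears. An illustrative two-arm simulation used 28 per arm, 28 sessions, a linear rise to 0.9 SD shared by pre and post readings, and an assumed 0.7 of variance between persons. The test of mean session change rejected in 5.5% of runs, about the nominal rate. The test of CVI-to-CVII change rejected in 99%.

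**4. Sessions treated as independent.** One-way illustration with four groups, 28 participants per group and 28 sessions each. The design effect is 1 + 27ρ.

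| Assumed ρ | Design effect | Simulated type I error |
|---|---|---|
| 0 | 1.00 | 0.05 |
| 0.05 | 2.35 | 0.355 |
| 0.10 | 3.70 | 0.557 |

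As a check, P(χ²₃ > 7.82 / design effect) gives 0.34 at ρ = 0.05 and 0.55 at ρ = 0.10. With only two values per participant, the simulated error is much lower: 0.079 at ρ = 0.1 and 0.157 at ρ = 0.5.

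**5. Two active-sham contrasts.** Unadjusted and independent: 1 − 0.95² = 0.0975. Power for d = 0.9 is below; each range runs from the two-group t-test to a contrast in a four-group model.

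| n per arm | alpha 0.05 | alpha 0.025 |
|---|---|---|
| 28 | 0.911–0.916 | 0.852–0.861 |
| 21 | 0.812–0.822 | 0.720–0.735 |

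**The case against.** - **The article labels no test as primary.** A reader might infer that these are the fixed primary-outcome tests. The text does not support that: it treats HRV and NRS together and offers alternatives. Contrasts may also be specified in a SAP that is not shown. This stands, but what the article does state still points to a different comparison from its question and its sample size.
- **The one-way option is described as repeated.** The natural reading is repeated-measures ANOVA, and random effects models are the named alternatives. A reader might infer that the plan carries the error rates in step 4. It does not; they apply only if sessions are analysed as independent. What remains is the two-way option, which has no such wording.
- **The visit change is calculated.** The phrase about differences in changes could be read to cover it, so a reader who concludes that the trial cannot detect a lasting effect goes too far. The fault is an unclear link between that change and a test.
- **Comparing the techniques is a stated aim.** The Abstract's Discussion and the scientific title set MNRB against tVNS. A reader might infer that this comparison should be dropped; the article does not support that. Still, the four-group test does not isolate it either.
- **Separate questions may each take 0.05.** This is defensible for two techniques, so 0.0975 is a fault only if the two contrasts form one claim. A larger family error that counts visit-level tests or contrasts is not supported, because the article states no such tests.

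**Conclusion.** The concern holds as a mismatch between question, sample size and stated tests. The firmest part needs no correlation assumption: the overall test can be significant from a modality difference alone. Its size, 57% with 28 per arm, rests on an assumed 0.5 SD difference. That within-session change is blind to an equal shift in both readings follows from algebra; the 5.5% and 99% are illustrative. The type I error figures of about 0.35 and 0.56 are conditional on independent-session analysis and on assumed correlations of 0.05 and 0.10, and a correctly specified mixed or repeated-measures model avoids them. The documents do not show that the trial cannot test against sham or that its error rate is inflated as planned. They show that the written tests, if followed, need not answer the first research question.

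**What to change.** 1. Name the CVI-to-CVII change in rMSSD as the primary analysis, on the log scale and adjusted for the CVI value. The CameraHRV section already makes rMSSD the main variable.
2. Test it by two contrasts: active against sham tVNS, and active against sham MNRB.
3. State whether 0.05 is shared across the two (Holm) or whether they are separate questions.
4. Analyse session changes as secondary, in a mixed model with a participant random effect and the same contrasts. Remove the ANOVA alternatives that lack a participant term.
5. Keep MNRB against tVNS as a stated secondary contrast, and do not use the four-group test to claim efficacy.

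The change is to analysis wording only. Recruitment was ongoing at submission and investigators get unblinded export only after database lock, so it can be made before unblinding. The price is power if alpha is split: at 0.025 per contrast and d = 0.9, about 0.85 to 0.86 with 28 per arm, but 0.72 to 0.74 with 21 completers, which is below the planned 0.8. Holm relaxes this for the second contrast once the first is significant.

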#### Description of intervention arms

##### Motivational Nondirective Resonance Breathing™ (MNRB™)

MNRB™ is a meditation-based deep breathing intervention developed by the lead author ([name]) [7] which is based on emergent findings in integrative neuroscience and autonomic self-regulation in cardiopulmonology.

Participants will perform MNRB™ at home for 15 min [61] in the morning upon waking and 15 min at night before going to bed (preferably at the same time for each individual participant) for a total duration of 2 weeks. Participants will use the BarTek™ device in order to practice MNRB™. The BarTek™ device is a CE-approved respiratory gating device compatible with an Android smartphone. Krüger&Matz Flow 5 Android smartphones will be used for running and recording the MNRB™ program with the BarTek™ respiratory gating device when practicing either active or sham MNRB™. Participants will receive MNRB™ user training at CVI and be provided with a BarTek™ operational worksheet which they will follow every morning and evening when practicing MNRB™.

(A)*Active MNRB™* will be practiced relaxed, sitting back in a chair no more than 30° from the horizontal, with both feet flat on the floor, hands on thighs with palms facing downward. Participants are further instructed to not talk or make any movements during their treatment session. The BarTek™ respiratory gating device is placed upon the diaphragm—around the abdomen, below the rib cage, and an inch (about two finger widths) above the navel. Participants open the MNRB™ program on the Krüger&Matz Flow 5 Android phone, which is connected wirelessly via Bluetooth to the BarTek™ respiratory gating device, and are guided through a 15 min MNRB™ breathing intervention which guides participants from an average respiration rate of 12 breadths/min to a resonance frequency rate of 6 breadths/min—the most optimal means of increasing cardiac-vagal tone (HRV) via respiration [47]. Out of a full (100%) breathing cycle, participants are instructed to use the stomach to breathe in to full inspiratory capacity for 30% and exhale for 60% by tightening and pulling the stomach back toward the spine. At the end of each inspiration and expiration, participants are instructed to retain their breadth for 5% of the cycle [62]. The participant is instructed to allow the chest to remain immobile throughout the entirety of the session [63, 64]. This is achieved through a feedback system actively engaging the patient to follow an orb that indicates stages of breathing and constantly correcting participants when they practice. While practicing, participants are to engage in a nondirective state of mind [65], where a relaxed focus of attention is established by listening to the inspiration and expiration sound guides of the MNRB™ program. Attention is neither directed toward staying with the respiration sound guides nor directed toward observing the spontaneous flow of thoughts and sensations [65]. Sensations, such as pain, during MNRB™ are accepted without actively directing attention toward them or away from them [7].

(B)*Sham MNRB™* is practiced relaxed, sitting back in a chair no more than 30° from the horizontal, with both feet flat on the floor, hands on thighs with palms facing upward. Participants are instructed not to talk or make any movements during their treatment session. Participants will be instructed to breathe at the normal respiration rate for an adult (12 breadths/min) [66] by following a respiratory pacer [67] on the Krüger&Matz Flow 5 Android MNRB™ program while counting their breadth [53]. Out of a full (100%) breathing cycle, participants are instructed to breathe normally with a 49% inhale and a 49% exhale without any (i.e., 1%) breath retention at the end of each inspiration and expiration. Participants are instructed to maintain a focused attention on their breath while actively detecting mind wandering [68].

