(A)*Active tVNS* is performed in a relaxed position, sitting back in a chair no more than 30° from the horizontal, with both feet flat on the floor, and hands on thighs with palms facing downward. The bipolar stimulation electrode is placed correctly within the concha of the left ear. Participants are instructed to breathe normally while not talking or making any movements during their session.(B)*Sham tVNS* is performed in a relaxed position, sitting back in a chair no more than 30° from the horizontal, with both feet flat on the floor, and hands on thighs with palms facing upward. The bipolar stimulation electrode is turned 180° and placed incorrectly over the center of the left earlobe instead of the outer auditory canal [15]. This area is known to be free of cutaneous vagal innervation [17] and produces no activation in the cortex and brain stem [15]. Participants are instructed to breathe normally while not talking or making any movements during their session.

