### Data collection procedure

#### Clinical visitations I and II (Fig. 6)

Testing administrators will conduct all data collection for CVI and CVII at the Department of Pain Management and Research under the supervision of the principal investigator. All data will be collected by the same assessor throughout each visitation. From 8:00 to 12:30, three participants will be consecutively registered upon arrival at the Department and directed to the clinical visitation room by an assigned testing administrator. Upon entering the visitation room, each participant will be given an informed consent and will be offered the time to ask any questions in regard to what is required of them for their participation. Upon signing the informed consent, measurements of height, weight, BMI, and WHR will be made. Participants will be instructed to remove any heavy clothing and footwear when on the digital electronic floor scale. BMI will be calculated as weight in kilograms divided by the square of the height in meters (kg/m^2^). After recording the aforementioned measurements, participants will sit in a relaxed semi-Fowler position (30° tilt from the horizontal) with feet flat on the floor, hands on thighs, and palms facing upward for the remainder of the clinical visitation. Any discrepancies to the procedure will be logged in Viedoc and kept for the remainder of the study period and will be included as a potential confounder in analyses.

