In order to acclimatize to the HRV recording environment, each participant is instructed to remain seated for at least 5 min [98] prior to taking the first HRV measurement (Fig. 7a). Acclimatization helps reduce HRV changes due to posture changes [99, 100] and can also reduce confounds subsequent to participant test anxiety [26]. Immediately following the 5 min acclimatization period, three 1-min HRV recordings will be taken on the tip of the right index finger of each participant separated by 1-min intervals. The beginning and end of each of the three HRV recordings will not be announced due to the impact of attentive states and test anxiety on respiratory frequency [101] and HRV recordings [102]. An average of the last two recordings will be used as the baseline measure.

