#### Daily intervention procedure (Fig. 8)

Upon waking or going to sleep, participants are to take a 1-min HRV recording with CameraHRV before and after their assigned 15-min treatment intervention. Participants are instructed to use the same HRV recording procedure as in CVI and CVII: sitting in a relaxed semi-Fowler position no more than 30° from the horizontal, knees at a 90° angle, while breathing normally, with both feet flat on the floor without moving or talking. Due to the fact that circadian rhythms and digestion have an impact upon HRV [107, 108], time of day and time since last meal should be standardized when possible in short-term HRV recordings, especially for designs incorporating repeated recordings over time [26]. Therefore, participants are instructed to take their HRV recordings preferably at the same time every day in the morning and at night before and after their assigned intervention. Furthermore, participants are instructed to keep a normal sleep schedule throughout their 2-week intervention while abstaining from consuming any large meals, caffeinated drinks, nicotine, or alcohol immediately prior to their morning HRV recordings and no less than 2 h before their evening HRV recordings. HRV recordings will be saved locally on the assigned Krüger&Matz Flow 5 phone and labeled with the participant’s assigned Viedoc identification number. Participants are to legibly encircle their NRS after each 1-min HRV recording (four times per day) in their Daily Treatment Journal throughout the 2-week intervention period.

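### Hand position during home sessions is tied to active versus sham in both modalities, just before the home post-session HRV reading

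*Protocol article*

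**What the plan says.** Under Description of intervention arms, hand position is specified separately for each arm:

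- Active MNRB: "with both feet flat on the floor, hands on thighs with palms facing downward".
- Sham MNRB: "with both feet flat on the floor, hands on thighs with palms facing upward".
- Active tVNS: "with both feet flat on the floor, and hands on thighs with palms facing downward".
- Sham tVNS: "with both feet flat on the floor, and hands on thighs with palms facing upward".

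At the clinic visits (Clinical visitations I and II), one position applies to everyone: "hands on thighs, and palms facing upward for the remainder of the clinical visitation". The same section requires at least 5 minutes seated before the first HRV recording and explains: "Acclimatization helps reduce HRV changes due to posture changes".

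At home (Daily intervention procedure), participants take a 1-minute HRV recording before and after each 15-minute session. The rule is: "Participants are instructed to use the same HRV recording procedure as in CVI and CVII". The posture list that follows covers back angle, knees, feet, breathing, movement and talking. It does not mention the palms.

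Statistical considerations and sample size calculation plans two kinds of HRV change: from the first to the second home data point over the 14 days, and from the first to the second clinic visit.

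**The concern.** A sham should match its active arm in everything except the ingredient under test. In this article those ingredients are the breathing pattern with its attentional instruction (MNRB) and the site of ear stimulation (tVNS). Palm orientation belongs to neither, yet it is set by arm, and in the same direction in both modalities. Pooling the modalities therefore does not balance it.

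The article treats posture as something to control for HRV. It fixes chair angle, feet and palms in clinic, requires a seated rest, and says departures from the visit procedure will be logged and considered as potential confounders. Assigning one posture element by arm does not fit that standard.

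At stake is how the home comparison can be read. If palm orientation in the preceding 15 minutes, or the change from it, had any influence on the post-session reading, that influence would be counted as treatment effect. Because everyone in an arm has the same instruction, no covariate adjustment could separate the two, and more participants or sessions would not reduce it.

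**Working it through.** The plan gives no figure for hand position, so the check compares the passages.

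**Step 1. Palm position by arm and setting.**

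| Setting | Active MNRB | Sham MNRB | Active tVNS | Sham tVNS |
|---|---|---|---|---|
| Home session, 15 min | down | up | down | up |
| Clinic HRV, both visits | up | up | up | up |
| Home HRV before and after session | clinic procedure by cross-reference; palms not named | same | same | same |

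In the first row, palm position predicts active versus sham without exception. The second row is the same for all arms. The third is one rule for all arms.

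**Step 2. What else differs in posture.** Nothing that the text states. All four arms sit back at the same maximum angle, feet flat, hands on thighs, without talking or moving.

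**Step 3. Which HRV contrast is touched.**

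- *Home, within session.* The missing-data rules number the daily recordings: first is morning before the session, second is morning after, third is evening before, fourth is evening after. The planned first-to-second change is thus a pre-to-post session change. The post-session reading directly follows 15 minutes in the arm-specific position. Exposed.
- *Clinic visit I to clinic visit II.* Recorded palms up in every arm after a seated rest. At visit I, HRV is recorded before the assigned treatment is introduced. Not exposed by this route.

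**Step 4. What the home recording rule implies for the palms.** There are two readings. If the cross-reference brings in the whole clinic procedure, palms are up at the reading and the active arms change from their session position. If only the posture list in that section applies, palms are unspecified and participants may keep the session position. On either reading, an arm-linked difference lies at or just before the post-session recording. The text does not say which is meant.

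**Step 5. A related mismatch.** Palms are to stay up for the rest of the clinic visit. Visit I also includes a 5-minute trial of the assigned treatment, which in the active arms is described as palms down. These passages need reconciling as well.

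**Step 6. Timing.** Trial status gives recruitment from 5 June 2019 to 1 August 2020 (366 + 57 = 423 days) and a protocol version dated 27 April 2020 (366 − 39 = 327 days after the start). 327/423 = 0.77, so about three quarters of the recruitment period had passed at that version date.

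**The case against.** A reader might infer that active participants change posture before the post-session reading while sham participants stay in the recording posture, so that the primary outcome is biased toward treatment. The documents do not support this.

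- The home rule prescribes one recording procedure for all arms. No different posture is prescribed at the reading itself.
- The reading is taken with the right index finger on the phone camera (CameraHRV section), and participants record it themselves. Sham participants therefore also have to move a hand.
- The clinic acclimatization rule concerns remaining seated. All four arms have been seated for 15 minutes in the same chair and foot position before the post-session reading. Applying the article's remark on posture changes to a turn of the palms is an inference.
- One cannot take palms up from the clinic cross-reference and also say that no settling period applies, since the same cross-reference would bring in the 5 minutes. The home steps are also shown in a figure and an operational worksheet that are not available here, so silence in the text is weak evidence.
- HRV change between clinic visits is also analysed, and this route leaves it untouched.

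It is also tempting to attach a false-positive rate. With 28 per group and no treatment effect, a two-sided t-test at 0.05 would reject in 6.6% of trials if the arm-linked shift were 0.1 SD of the HRV change, and in 11.4% if it were 0.2 SD. Those shifts are pure assumptions: the article gives neither a size nor a sign, and a shift the other way could hide a benefit. They illustrate the mechanism and do not estimate a bias.

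All of these objections stand, and they limit the reach of the point. They leave its core intact: palm position is specified, differs by allocation in both modalities, and has no stated purpose.

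**Conclusion.** The point holds in a narrow form and is of low severity. Hand position during sessions is fully confounded with active versus sham allocation in both modalities, and the text on home HRV recording does not name the palm position. Any consequence is confined to the home within-session HRV comparison. The visit-to-visit HRV comparison is not affected by this route.

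No size can be given. The effect may be small or nil, and it could create or conceal a difference. The conclusion rests on the arm descriptions being followed as written, and on the first-to-second home change being the pre-to-post session change, as the numbering of recordings indicates. It does not show that the primary outcome is biased.

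**What to change.** Use the same hand position in all four arms, and name it in the home HRV recording instruction. Bring the four arm descriptions, the clinic visit procedure and the daily intervention procedure into line, including the 5-minute treatment trial at the first visit. Choosing the position already used for clinic HRV would avoid a further change between session and reading; the choice is for the investigators. Update the participant worksheets to match.

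For participants already treated, report the difference in hand position as a limitation of the within-session HRV comparison.

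The cost is one line in each instruction sheet. The downside is that a minor instruction would differ between participants before and after the change, late in recruitment. If few participants remain to be enrolled, the limitation statement alone may be the proportionate step.
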